## Abstract

**Background:**

Substance use is among the main contributors to disease among children and adolescents in the Americas region. The call for effective prevention of substance use among adolescents has resulted in numerous school-based programs, and particularly the Unplugged program has been proved to be successful in reducing the prevalence of different substances in seven European countries. The purpose of this study is to test the effectiveness of the Unplugged program in Chile (“Yo Sé Lo Que Quiero”).

**Methods:**

This is a cluster randomized controlled trial, parallel-group type, where “Yo Sé Lo Que Quiero” is compared to standard school preventive curricula in control schools. A total of 70 schools and 8400 adolescents are expected to be randomized with 1:1 allocation. During formative work, the Unplugged program was culturally adapted to Chile, and the instrument to assess the primary and secondary outcomes was validated. The effectiveness of this program will be assessed using the European Drug Addiction Prevention Trial Questionnaire (EU-Dap), measuring substance use prevalence and risk and protective factors in baseline, post-intervention, and four months after the end of the intervention.

**Discussion:**

The proposed study will be the first to test the effectiveness of a school-based substance use prevention program in Chile in a cluster randomized control trial and the first study evaluating the Unplugged program in Spanish-speaking Latin America. A model for disseminating the Unplugged program inside Europe already exists and has been implemented successfully in several countries. Thus, if the effects of the program are positive, wide implementation in Chile and Latin American countries is possible soon.

**Trial registration:**

ClinicalTrials.govNCT04236999. Registered on January 17, 2020.

## Administrative information

Note: the numbers in curly brackets in this protocol refer to SPIRIT checklist item numbers. The order of the items has been modified to group similar items (see http://www.equator-network.org/reporting-guidelines/spirit-2013-statement-defining-standard-protocol-items-for-clinical-trials/).

## Introduction

### Background and rationale {6a}

Substance use and mental disorders are among the main contributors to disease among children and adolescents in the Americas region, representing 5.2% of the disability-adjusted life years (DALYs) and 17.2% of the years lived with a disability (YLD) in the population from 0 to 14 years [1]. In 2015, Chile led this region in tobacco use in the last month among adolescents in secondary education, reaching a prevalence of 23.7% [2]. Regarding the prevalence of marijuana use in the last year among adolescents in secondary education, Chile also led with 32.8% [2]. It should be noted that this last indicator has almost doubled in the last two decades from 14.8% in 2001 to 26.8% in 2019 [3]. Regarding the prevalence of alcohol use in the last month among secondary school adolescents, it has remained relatively stable during the last two decades, being 38.9% in 2011 and 29.8% in 2019 [3].

On the other hand, currently, the world is facing a COVID-19 pandemic, which has caused widespread disruptions in the lives of adolescents and their families, however to date, little is known about the pandemic’s unfolding impact on adolescent’s substance use [4]. It can only be mentioned one longitudinal study conducted in Iceland [4] where the results showed a decrease in substance use during the pandemic among adolescents as compared with pre-pandemic figures. The authors mentioned it might be attributed to an unintended benefit of the isolation during lockdowns.

Substance use among adolescents has been associated with the onset of psychiatric disorders such as depression and anxiety disorders [5, 6] in addition to dependency and substance abuse [6, 7], and it is known that the earlier in life the onset of substance consumption, the greater the risk of dependence in the future [8, 9]. The potential explanation of these findings is related to the crucial brain development on cognitive, behavioral, and mood functions that occur during adolescence [10–13].

The call for effective prevention of substance use among adolescents has resulted in numerous school-based programs developed for this purpose. For instance, a systematic review shows that the implementation of these programs has protective effects in the prevention of substance abuse [14]. A meta-analysis examining the effectiveness of interactive high school drug prevention programs on adolescent marijuana use in North America [15] shows that programs such as “Project ALERT,” “Life Skills Training,” and “All Stars” can potentially delay or prevent adolescent marijuana use. Additionally, a systematic review of European studies [16] highlighted another program called “Unplugged” implemented in seven countries, where positive results were obtained three months after the end of the intervention and 18 months later. Among these findings, there was a decrease in the frequency of drunkenness and cannabis use compared to controls [17].

Carrying out such research in Chile, where there is an urgent need for evidence-based prevention of substance use, is highly relevant. For example, nowadays, the government with the National Service for the Prevention and Rehabilitation of Drugs and Alcohol (SENDA) have a national program called “Elige Vivir Sin Drogas” in collaboration with the Icelandic Centre for Social Research and Analysis (ICSRA) and the application of the Planet Youth survey among adolescents attending year 10 [18]. This survey collects local information about risk and protective factors and substance use. Later, the results are presented to the local authorities, who have to design and implement preventive interventions. However, no randomized controlled trials (RCT) have been carried out in Chile to test the effectiveness of existing substance use prevention programs among adolescents. Therefore, without evidence-based preventive interventions, it will be difficult to change the current prevalence of this problem. The available programs in Chile are those developed, but not evaluated, by the government, such as “Continuo Preventivo,” which includes three programs “Descubriendo el gran Tesoro” (preschool students and parents/tutors), “Aprendemos a crecer” (1st to 4th grades students), and “La decision es nuestra” (7th to 12th grades students). In addition, there are a few independent initiatives such as the program “Familias Fuertes: Amor y límites,” developed by the Pan American Health Organization (PAHO), which has been implemented and evaluated in Chile [19], using a quasi-experimental design. This program intervened among adolescents and their parents in seven educational sessions. After six months, the results showed differences in parental styles but no change in reducing risk behaviors among adolescents.

The Unplugged program is a school-based intervention for the prevention of substance use in junior high schools, first implemented in seven European countries (Austria, Belgium, Germany, Greece, Italy, Spain, and Sweden). The Unplugged program targets students of 12–14 years old, and it has an aim to tackle both experimental and regular use of tobacco, alcohol, and illegal drugs. The curriculum is based on a comprehensive social influence approach, incorporating components of life skills into a Cognitive Social Influence model [20]. Special emphasis is given to the correction of normative beliefs about drugs and drug use. This program is organized in 12 sessions around three themes: (1) Knowledge and attitudes (1–4 sessions): students reflect on their knowledge on legal and illegal drugs, using tests to reach an objective assessment of this knowledge. These sessions also help students to make a distinction between desirable and undesirable consequences of taken drugs and between risk and protective factors. The program includes several interactive activities to facilitate the acquisition of this objective knowledge using several sources; (2) Intrapersonal skills (5–6 sessions): students reflect on normative beliefs, where perceived prevalence of drug use at students’ age is compared with the actual local prevalence, helping to develop critical thinking. Several role-play activities help to discuss peer-group attachment, group approach, peer-group allowance, and peer-group expectations. There are other interactive activities about emotion expression and positive ways to communicate and receive feedback; and (3) Interpersonal skills (7–12 sessions): students are instructed to practice refusal skills, assertiveness, and analyze coping strategies. They are also instructed and practice how to make decisions using a five-step model.

The effectiveness of this program was assessed by its authors over time; In 2010, the intervention was associated with a reduction in the prevalence of drunkenness episodes of around 38% and 26% in the use of marijuana in the last 30 days [17]. In 2011 it was shown to be associated with a decreased risk of reporting alcohol-related problems [21]. And in 2014, it was analyzed that after the intervention, there was a lower prevalence of drunkenness episodes and the intention to get drunk in students who attended schools with a low socioeconomic level [22].

In this study, we will adapt the Unplugged program for schools in Chile (henceforth in Chile “Yo Sé Lo Que Quiero,” YSLQQ), evaluating its effectiveness in this new context. Besides its huge practical significance, the project will contribute to the scientific discussion on the replicability of substance use school-based prevention programs in new contexts.

### Objectives {7}

The main objective of this study is to develop a culturally appropriate version of an evidence-based substance use prevention program called Unplugged, adapted to the Chilean culture (YSLQQ), and to test its effectiveness among early adolescents in primary schools in Santiago, Chile.

There are two stages in this study, formative work and the study of the effectiveness of the program. The specific objectives regarding formative work are the following: (1) To obtain the training in the Unplugged program from the developers. The approval for using the program in Chile is already granted, and the training of the research team was conducted at the beginning of the project (2018–2019); (2) To review the available Spanish version of the Unplugged program and culturally adapt it to Chile. This work was finished during 2019-2020; (3) To pilot the preliminary version of the cultural adaptation of the Unplugged program. This pilot acceptability and feasibility study were conducted in 2019, and the results are under analysis, and the article is in the writing process. (4) To pilot and validate the instruments that will be used to assess the effectiveness of the intervention. This validation was performed in 2018, and the results are submitted and under review. (5) Finally, the final stage is conducting a cluster randomized controlled trial to test the effectiveness of the program. The specific objective of this stage is (1) to compare the level of self-reported substance use of 6th and 7th graders participating in the YSLQQ program and control schools immediately after the end of the intervention and four months later, controlling by baseline assessment. This study will be carried out in 2022 and 2023, and we present its protocol here.

We hypothesize that at the end of the intervention, there will be a lower proportion of students who have initiated substance use and a lower proportion of students who have passed from experimental use to regular use of tobacco, alcohol, and cannabis in schools who received “Yo Sé Lo Que Quiero” when compared to standard school drug prevention curricula in control schools.

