### Outcomes {12}

#### Primary outcome

Regular alcohol use measured with the European Drug Addiction Prevention Trial Questionnaire (EU-Dap) validated in Chile (manuscript under revision). Regular alcohol use is defined as the prevalence of any alcohol use during the last 30 days previous to the survey.

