#### Secondary outcomes

Prevalence of substance use:Tobacco use: Tobacco use will be evaluated with two variables: 12-month tobacco use prevalence and 30-day tobacco use prevalence.Alcohol heavy use: Drunkenness will be evaluated with two variables: 12-month drunkenness prevalence and 30-day drunkenness prevalence.Marijuana: Marijuana use will be evaluated with two variables: 12-month marijuana use prevalence and 30-day marijuana use prevalence.(2)Knowledge and skills promoted by the YSLQQ program:Positive and negative beliefs about tobacco use (no. of items = 8, e.g., How likely is that each of the following would happen to you if you smoke cigarettes in the next month? (v) Feel more relaxed; Answers 1= *Very unlikely* to 4= *Very likely*)Positive and negative beliefs about alcohol use (no. of items = 10, e.g., How likely is that each of the following would happen to you if you drink alcohol in the next month? (i) Do badly in school; Answers 1= *Very unlikely* to 4= *Very likely*).Positive and negative beliefs about marijuana use (no. of items = 10, e.g., How likely is that each of the following would happen to you if you take marijuana in the next month? (vi) Have more fun; Answers 1= *Very unlikely* to 4= *Very likely*).Positive and negative attitudes towards drugs (no. of items = 11, e.g., Here are some statements that people have made about illegal substances. How much do you agree with the following opinions on drugs? (iii) Using drugs is fun; Answers 1= *Strongly disagree* to 4= *Strongly agree*).Knowledge about substances (no. of items = 6, e.g. (i) Nicotine is the substance in cigarettes that causes lung cancer; Answers 1= *Yes*, 2= *No, 3= Don’t know*).Normative beliefs [perception of the number of user friends] (no. of items = 5, e.g., When you answer this question, think about the friends with whom you spend most of your leisure time. (iv) How many of them get drunk?; Answers 1= *None* to 5= *All of them*).Refusal skills (no. of items = 3, e.g. (i) You and your best friend are at a party where you meet new people, and you feel you really want to get to know them. Someone offers you to smoke hash together. Your friend accepts. Do you?; Answers 1= *Very unlikely* to 4= *Very likely*).School bonding (no. of items = 5, e.g., How much do you agree with the following descriptions of your school? (i) The students in my class enjoy being together; Answers 1= *Strongly disagree* to 4= *Strongly agree*).Decision-making skills (n. of items = 5, e.g., There are several possible ways to make decisions. How well do the following apply to you? (iv) I often regret something that I had decided; Answers 1= *Strongly disagree* to 4= *Strongly agree*).

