## Statistical methods

### Statistical methods for primary and secondary outcomes {20a}

General school features (size, number of teachers, etc.) will be used to compare participating schools with the ones that were invited but did not participate. Additionally, descriptive statistics will be used to compare the two arms at baseline.

Primary and secondary analysis will be conducted on an intention-to-treat basis. Odds ratios (OR) and their corresponding confidence intervals (95%CI) will be calculated as the measure of association between experimental condition (Intervention arm) and behavioral outcome, controlling for baseline outcome variable scores. Secondary analysis will be conducted considering adjustment for variables with marked imbalance at baseline. Additionally, secondary analyses will be made using the secondary outcomes and analyzed with the same approach. To take into account the hierarchical structure of the data and the cluster effect, a multilevel modeling approach will be followed in the analysis of the data. Data will be analyzed with Stata 17.0.

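### The hypothesis about initiation and progression to regular use is not tested by the outcomes and analysis as written: every substance-use outcome is a whole-sample prevalence, and regular alcohol use means any drinking in 30 days

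*Protocol article*

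**What the plan says.** The protocol article, Objectives {7}, gives two statements for the trial stage.

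- The specific objective is "to compare the level of self-reported substance use of 6th and 7th graders participating in the YSLQQ program and control schools", after the intervention and four months later, with control for baseline.
- The hypothesis, which follows it, has two parts. The first concerns initiation: "there will be a lower proportion of students who have initiated substance use". The second concerns progression among those who already use: "a lower proportion of students who have passed from experimental use to regular use of tobacco, alcohol, and cannabis".

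The Primary outcome section states: "Regular alcohol use is defined as the prevalence of any alcohol use during the last 30 days previous to the survey". The Secondary outcomes section lists six further substance-use variables: "12-month tobacco use prevalence and 30-day tobacco use prevalence", "12-month drunkenness prevalence and 30-day drunkenness prevalence" and "12-month marijuana use prevalence and 30-day marijuana use prevalence". It also lists nine measures of beliefs, attitudes, knowledge, school bonding and skills.

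Statistical methods {20a} plans odds ratios from a multilevel model, "controlling for baseline outcome variable scores". The subgroup analyses in {20b} are by sex and by grade.

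**The concern.** The hypothesis is about changes of state: from not using to using, and from experimental to regular use. The substance-use outcomes describe a state at one time. A student who first tasted alcohol the week before the survey and a student who drinks every weekend score the same on the primary outcome, and both are labelled regular users. A student already drinking at baseline who carries on also scores the same as one who has just started.

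What is at stake is the claim. A lower 30-day prevalence reported against this hypothesis would be read as prevention of initiation and of progression to regular use, and neither follows from the analysis. The Discussion links positive effects to wide implementation in Chile and other Latin American countries, so the exact content of the claim matters.

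**Working it through.** **1. Hypothesis set against outcomes.**

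| Substance | Listed use outcomes | New use among baseline non-users | Experimental to regular |
|---|---|---|---|
| Alcohol (use) | 30-day (primary) | not defined | not defined |
| Alcohol (drunkenness) | 12-month, 30-day | not defined | not defined |
| Tobacco | 12-month, 30-day | not defined | not defined |
| Marijuana | 12-month, 30-day | not defined | not defined |

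That is 1 + 6 = 7 prevalences and no transition. Alcohol has no listed 12-month or lifetime use variable, so earlier but not recent drinking is not captured by any listed outcome.

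**2. Whether the 12-month items stand in for initiation.** Twelve weekly sessions last about 3 months. Adding 4 months of follow-up gives about 7 months. If sessions run weekly without long breaks, 12-month recall at both follow-ups reaches back before the program and counts earlier use.

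**3. Whether baseline adjustment separates the parts.** Let b be the baseline 30-day prevalence, c the share of baseline users still using at follow-up, and i the share of baseline non-users now using. Follow-up prevalence is P = b·c + (1 − b)·i, so the arm difference is b·Δc + (1 − b)·Δi. One odds ratio adjusted for baseline pools the two terms.

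The article gives no baseline rate. Taking b = 4.18% (the planning rate, as an assumption), the planned 2-point difference could arise from:

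- continuing users only: Δc = 0.02 / 0.0418 = 0.48, a fall of 48 percentage points;
- new users only: Δi = 0.02 / 0.9582 = 0.021, a fall of 2.1 percentage points.

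If b is below 2%, continuing users alone cannot produce 2 points. At the planned rates, then, most of such an effect would plausibly be new 30-day use. But a baseline 30-day non-user need not be a never-user, so Δi still mixes first use with resumed use.

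**4. The plan's own figure.** Inputs from Sample size {14}: 4.18% against 2.18%, two-sided alpha 0.05, power 0.80, ICC 0.02. School size is 4200 / 35 = 120, which is four classes of 30.

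- n = [1.96·√(2·0.0318·0.9682) + 0.842·√(0.0418·0.9582 + 0.0218·0.9782)]² / 0.02² = 1208 per arm
- design effect = 1 + (120 − 1)·0.02 = 3.38
- 1208 × 3.38 = 4083, which rounds up to 35 schools × 120 = 4200 per arm, with power about 0.81

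The stated size reproduces, and it is built on whole-sample 30-day alcohol prevalence.

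**5. Precision of transition analyses (illustration only).** The article gives no initiation or progression rate. The assumptions are the same relative effect (2.18 / 4.18 = 0.52), ICC 0.02 and 4200 per arm. For a subset with share s, the effective n is 4200·s / [1 + (120·s − 1)·0.02].

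- New use, s = 97% to 99%: power about 0.49, 0.67 and 0.79 at control rates of 2%, 3% and 4%.
- Progression, s = 5% (210 per arm, effective 191): power 0.42, 0.74 and 0.92 at control rates of 10%, 20% and 30%.
- Progression, s = 10% (420 per arm, effective 344): power 0.66, 0.94 and 0.995 at the same rates.

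**The case against.** The strongest reply is that only one sentence is out of line. The specific objective, the primary outcome, the sample size and the baseline-adjusted model all concern level of use and fit together. *Regular* is given an explicit definition, so the tested quantity is not ambiguous. If baseline use is no higher than 4.18%, about 96% of students start as non-users on the primary outcome, and baseline users can have only limited influence. Exact transition definitions could also sit in a full protocol or SAP that is not shown.

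Much of this stands. The primary test is coherent, and missing detail on transition analyses is not the point raised here. What remains is that the hypothesis and the outcomes are both stated in this article and do not match. A later plan could add analyses, but the hypothesis and the label would still be misaligned. Defining *regular* as any recent use also removes the contrast with experimental use on which the hypothesis depends.

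A reader might go further and infer that the hypothesis cannot be tested at all, or that every outcome is a prevalence. The article does not support either. Students are assessed at baseline and twice afterwards and carry individual ID numbers (Data management {19}), so some transitions can be derived. Nine of the secondary outcomes are not prevalences.

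**Conclusion.** The concern holds as a mismatch between the stated hypothesis and what the plan tests. Neither initiation nor progression is isolated for any of the three substances by the seven substance-use outcomes, the pooled odds ratio or the sex and grade subgroups. The gap is widest for alcohol, the primary substance, where no listed variable records earlier but not recent use.

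It does not reach the validity of the primary comparison or the 4200 per arm, and a reader should not infer that either is undermined. Nor do the documents show that a positive result would come from baseline users stopping. At the planning rates that would take a 48-point fall in continued use, and this figure rests on an assumed baseline prevalence. The consequence is a limit on what may be concluded.

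**What to change.** 1. Call the primary outcome past-30-day alcohol use, and restate the confirmatory hypothesis as a lower past-30-day prevalence in program schools, in line with the specific objective.
2. Add secondary analyses on the linked baseline and follow-up questionnaires. For each substance, analyse 30-day use at follow-up among baseline 30-day non-users, described as new 30-day use because it may include resumed use. Where the questionnaire has a 12-month or lifetime item, also analyse 30-day use at follow-up among students with earlier but no 30-day use at baseline. Such an item is listed for tobacco and marijuana. For alcohol it is not confirmed in the article and should be checked first.
3. Limit conclusions on initiation or progression to those analyses.

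The first and third changes cost only wording. The second uses data the trial already plans to collect, apart from the alcohol item to be checked. It adds a few secondary outcomes, and the progression subset is likely to be small and imprecise. The sample size needs no change.
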